# Shenmai injection for the treatment of cancer-related fatigue in advanced non-small cell lung cancer patients undergoing chemotherapy: study protocol for a randomized controlled trial

**DOI:** 10.1186/s13063-018-2845-7

**Published:** 2018-09-04

**Keywords:** Traditional Chinese medicine, Cancer-related fatigue, Non-small cell lung cancer, Shenmai injection, Randomized controlled trial

## Abstract

**Background:**

Cancer-related fatigue (CRF) is the most common symptom in patients with advanced non-small cell lung cancer (NSCLC) undergoing treatment with chemotherapy. However, evidence upon which to base management strategies is scarce. Traditional Chinese Medicine (TCM) has been shown to be beneficial to patients with CRF. Chinese herbal injections should be administered under an evidence-based approach. This trial aims to assess the efficacy and safety of the addition of the Shenmai injection (SMI) to conventional therapy for CRF in NSCLC patients undergoing chemotherapy.

**Methods/design:**

The study is a two-group, prospective, randomized controlled trial (RCT) designed to evaluate the efficacy and safety of SMI for CRF NSCLC patients undergoing chemotherapy. Eligible participants will be randomized to either a treatment group receiving a 5-day Shenmai injection regimen plus conventional therapy or a control group receiving only conventional therapy. The primary outcome is fatigue, assessed using severity scores from the Functional Assessment for Chronic Illness Therapy-Fatigue (FACIT-F) measurement system. Secondary outcomes include symptom distress scores, depression, sleep disorders, quality of life, and levels of immunologic indicators. Assessments will be carried out at baseline and on day 5 (the end of the intervention).

**Discussion:**

This study can provide evidence to support clinical decision-making in the management of CRF in NSCLC patients undergoing chemotherapy in a way that can be scaled up and used throughout China.

**Trial registration:**

Chinese Clinical Trial Registry (chictr.org.cn), ChiCTR-INR-17013737. Registered on 6 December 2017.

**Electronic supplementary material:**

The online version of this article (10.1186/s13063-018-2845-7) contains supplementary material, which is available to authorized users.

## Background

Lung cancer is the leading cause of cancer-related mortality worldwide [1]. Chemotherapy remains the primary treatment for non-small cell lung cancer (NSCLC) patients. A history of chemotherapy was independently associated with severe cancer-related fatigue (CRF) in patients with various types of advanced cancer [2]. Chemotherapy has considerable toxicity, which is a significant factor in the severe fatigue often experienced by cancer patients. Fatigue, in turn, can become a dose-limiting factor during chemotherapy.

CRF has been defined by a panel of the National Comprehensive Cancer Network (NCCN) as a persistent, subjective sense of tiredness related to cancer or cancer treatment that interferes with usual functioning [3]. One of the characteristics of CRF that distinguishes it from other types of fatigue is that it is not relieved by sleep or rest [3–5], and patients report being “unusually” or overwhelmingly tired [3–6].

Cancer patients undergoing aggressive therapy and those with advanced disease often experience clusters of severe symptoms led by fatigue. CRF most commonly occurs with other symptoms, such as depression, anxiety, pain, sleep disorder, and loss of functional status [7]. Overall 50–90% of people with cancer experience fatigue [8–10]. CRF profoundly impacts on a person’s physical, emotional, and mental well-being [11]. It has a clear negative impact on the quality of life of people with cancer and their ability to maintain their usual personal, professional, and social relationships [12].

The development of fatigue occurs alongside other symptoms, such as pain, distress, poor appetite, drowsiness, and disturbed sleep. It provides a rationale for studying the role of inflammation as a common mechanism underlying the production of multiple symptoms, including fatigue.

The hypothesis that activation of the proinflammatory cytokine network induces fatigue has been under investigation since the 1990s. Dysregulated inflammation and its toxic downstream effects are believed to constitute a significant biological basis for CRF and other symptoms [13–15]. Preclinical research on immune-to-brain communication pathways in the peripheral immune system indicates that proinflammatory cytokines, primarily interleukin (IL)-1β and tumor necrosis factor (TNF)-α, send signals to the brain that promote symptoms associated with sickness, including fatigue, disturbed sleep, and depressive symptoms in vulnerable individuals. TNF-α has been found to be a prognostic inflammatory biomarker of persistent fatigue [16]. TNF-α signaling has been associated with postchemotherapy fatigue in patients with early-stage breast cancer [17].

Despite the frequency of CRF in cancer patients and various pharmacologic and nonpharmacological approaches that have been studied, it still remains underdiagnosed and undertreated, partly because of limited understanding of its pathophysiology and lack of effective treatments [18, 19].

Chinese herbal medicine has been widely used in the treatment of people with cancer in China [20]. Studies have shown that Chinese herbal medicine has beneficial effects on assisting in treating cancer, retarding cancer progression, boosting the immune system, and ameliorating chemotherapy-induced complications and side effects, such as pain and fatigue [21, 22].

Shenmai injection (SMI), derived from the famous traditional Chinese herbal prescription Shendongyin which is described in the *Zheng Yin Mai Zhi* [23] by Qin Changyu in the Ming dynasty, is extracted from red ginseng (*Radix ginseng Rubra*) and dwarf lilyturf tuber (*Radix ophiopogonis*). It has been widely used in traditional medicine in China and has been developed as a traditional Chinese patent drug based on the national standards approved by the CFDA (China Food and Drug Administration) since 1995.

In traditional Chinese medicine (TCM), *qi* usually refers to life energy, which manifests simultaneously on the physical and mental-spiritual levels [24]. The quintessence of TCM is syndrome differentiation and treatment. From the perspective of TCM, CRF is recognized as deficiency syndrome pattern, which is mainly caused by deficiency of *qi* and disharmony of *yin* and *yang* [25]. Many patients with CRF have symptoms of fatigue, listlessness, shortness of breath, and weak pulse after chemotherapy. These symptoms are similar to the syndrome of *qi* deficiency in TCM theory. According to TCM theory, this herbal prescription has been identified as an effective medication to tonify *qi* for reducing general weakness [23].

Ginsenosides, extracted from ginseng, and ophiopogonis, extracted from dwarf lilyturf tuber, are the principal constituents responsible for the pharmacological activities in SMI [26]. There are several studies on ginseng for the treatment of fatigue, and studies in mice have shown that ginseng can alleviate fatigue [27, 28]. One large study evaluating ginseng in combination with vitamins and minerals in 232 patients who had functional fatigue for over 10 years concluded that the ginseng formula improved fatigue symptom scores statistically significantly more than vitamin placebo [29]. An abstract presented at the 2003 meeting of the American Society of Clinical Oncology evaluated ginseng in people with cancer. It reported that ginseng significantly improved total and average fatigue levels, even though the sample size was quite small (*n* = 20) [30].

This study aims to assess the efficacy and safety of the addition of SMI to conventional therapy for advanced NSCLC patients undergoing chemotherapy. The primary hypothesis is that the SMI plus conventional therapy (here our treatment group) will experience less fatigue, as measured using Functional Assessment for Chronic Illness Therapy-Fatigue (FACIT-F) subscale scores, than conventional therapy alone (here our control group). Secondary objectives are to evaluate the efficacy of SMI on the following factors: symptom distress scores, depression, sleep disorders, quality of life (QOL), levels of inflammatory indicators, and adverse events (AEs).

## Methods/design

### Design

This study is registered on chictr.org.cn (ChiCTR-INR-17013737). A brief flowchart of the entire study is shown in Fig. 1, and the schedule of events is provided in Fig. 2. This will be a two-group, prospective, randomized controlled trial (RCT) to evaluate the efficacy and safety of SMI for CRF NSCLC patients undergoing chemotherapy. Eligible participants will be randomized to either a treatment group receiving a 5-day SMI regimen plus conventional therapy or a control group receiving only the conventional therapy. The protocol includes the recommended elements elaborated upon in the Standard Protocol Items: Recommendations for Interventional Trials (SPIRIT) [31] checklist (Additional file 1).

**Fig. 1 Fig1:**
[figure not shown]
Study design flow chart. iv. intravenous, SMI Shenmai injection

**Fig. 2 Fig2:**
[figure not shown]
Treatment schedule and outcome measures. D day, SMI Shenmai injection

### Setting and participants

The study will be conducted in Guangzhou, the third largest city in southeastern China. Patients will be recruited from the oncology inpatient department at each of the three GPHCM branch hospitals in the different urban districts of Guangzhou. A complete list of inclusion and exclusion criteria is provided in the following section.

### Randomization, allocation concealment, and blinding

Patients who provide informed consent will be randomized into either a treatment group receiving a 5-day SMI regimen plus conventional therapy or a control group receiving only the conventional therapy. A block randomization sequence will be generated by SAS 9.2 (SAS Institute Inc., Cary, NC, USA) in a 1:1 ratio. Treatment assignments will be conducted using a web-based allocation system. Given the nature of the intervention, it is impossible to blind the patients and personnel involved in conducting the programs. Outcome assessors, laboratory technicians, data managers, and statisticians will be unaware of the treatment allocations.

### TCM syndrome pattern differentiation

The diagnosis as described in TCM, deficiency of *qi* syndrome pattern, will be based on guidelines delineated in the Clinical Research of New Investigational Drugs in Traditional Chinese Medicine [32]. The diagnostic criteria are as follows: 1) primary signs and symptoms include fatigue, listlessness, shortness of breath and weak pulse; and 2) secondary signs and symptoms include soreness of the lower back and knees, spontaneous perspiration, and pale lips.

Participants will be diagnosed with deficiency of *qi* syndrome if they have two or more of the primary signs or symptoms, at least one of the secondary signs or symptoms, and examination of the tongue and pulse indicates deficiency of *qi*. After being screened for inclusion and exclusion criteria, eligible patients will be entered into the trial.

### Eligibility criteria

#### Inclusion criteria

Participants who meet the following criteria are eligible:Patients with histologically or cytologically confirmed NSCLC who are undergoing chemotherapy;Clinical stage IIIB, IIIC, or IV;Clinically confirmed CRF at a score of ≥ 4 on the Edmonton Symptom Assessment Scale (ESAS; scale of 0 to 10) within the past 24 h;Chinese syndrome differentiation of *qi* deficiency;Aged between 18 and 75 years;Eastern Cooperative Oncology Group (ECOG) performance status score 1 and 2;Able to read Chinese and willingness to provide signed informed consent;Hemoglobin ≥ 90 g/L.

#### Exclusion criteria

Exclusion criteria are as follows:Active double cancer;Severe mental disorder (severe anxiety, depression, or cognitive dysfunction);Severe central nervous system metastasis or acute disease interfering with attendance for therapy;Impaired hepatic (alanine aminotransferase level ≥ 80 IU/L) or renal (creatinine level ≥ 2 mg/dL) function;Received erythropoietin (EPO) and proprietary Chinese medicine reinforcing *qi* orally or intravenously;A history of hypersensitivity to the components of the trial medication;Pregnant or lactating women;Unable to understand or sign an informed consent form.

### Interventions and control

The treatment delivery processes for both the intervention and control groups are outlined in Fig. 2.

#### Control group

Patients in the control group will receive only conventional therapy according to national guidelines.

#### Intervention group

Patients in the treatment group will receive a 5-day Shenmai injection regimen plus conventional therapy. According to national guidelines, conventional therapy includes the routine use of antiemetic and gastro-protective agents. SMI will be manufactured by Huarun Ya’an Sanjiu Pharmaceutical Co., Ltd., based on good manufacturing practice (GMP) standards. Each milliliter of the injection is equivalent to 0.1 g of red ginseng (*Radix ginseng Rubra*) and 0.1 g dwarf lilyturf tuber (*Radix ophiopogonis*) of crude drug. It will be administered at a dose of 100 ml by intravenous infusion once daily for 5 days as a period. Treatment will be administered by Chinese medicine physicians with 5 years of formal university training in Chinese medicine, a license to administer treatment, and at least 1 year of clinical experience.

### Data collection

The study data collection process is outlined in Fig. 2.

### Baseline data

The following baseline data will be collected using questionnaires and a review of medical charts: 1) sociodemographics; 2) medical history; and 3) anthropometric variables.

### Outcome measures and assessments

Each participant will be asked to attend an in-person assessment appointment at the GPHCM Oncology Department at two time points: baseline and day 5 (the end of the intervention). During each assessment, participants will be asked to complete specified physiological tests and self-reported questionnaires. All tests will be administered by one of two trained independent assessors.

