### Primary outcome

#### Fatigue severity

Fatigue severity will be self-assessed using the Functional Assessment for Chronic Illness Therapy-Fatigue (FACIT-F) subscale at baseline and on day 5. FACIT-F is a well-validated quality-of-life instrument widely used for the assessment of CRF in clinical trials. It consists of 27 general quality-of-life questions divided into four domains (physical, social, emotional, and functional) and the 13-item FACIT-F fatigue subscale [33]. FACIT-F allows patients to rate the intensity of their fatigue and its related symptoms on a scale of 0 to 4 (0, not at all; 4, very much). The total score for FACIT-F is the sum of the four domains (physical, social, emotional, and functional) plus the fatigue subscale.

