### Sample size estimation

The primary endpoint is the fatigue severity self-assessed using the FACIT-F subscale. The sample size is calculated based on the primary endpoint. Previous clinical practice suggests a mean difference (MD) of 4.95 between groups, and the same standard deviation (SD) of 7.28 for each group. Using a superiority test, it is estimated that 38 participants per group are needed to achieve 90% power and a (two-sided) 5% significance level in detecting treatment differences. Thus, the final sample size has been set at a total of 94 patients (47 in each group), assuming a 20% dropout rate.

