Data will be entered using the double-entry method. Data quality will be checked regularly by research assistants and overseen by monitors. Data monitoring will be conducted regularly with standard operation procedures by a team from the GPHCM Key Unit of Methodology in Clinical Research. Inspections will be performed regularly by the GPHCM Department of Science Research. All modifications are to be marked on the case report forms. Data managers will then recheck the data before logging it. The database will be locked after all data have been cleaned. If participants withdraw from the trial during the study period the reasons must be documented, and the dropout rate is to be statistically analyzed.

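### One in-person day-5 appointment is the only post-baseline source of the primary outcome, with no stated backup and with dropouts excluded, so loss of the score can differ by arm and bias the comparison in either direction.

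*Protocol article*

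**What the plan says.** All references are to the protocol article.

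- **Timing and mode.** The section Outcome measures and assessments fixes both: "Each participant will be asked to attend an in-person assessment appointment at the GPHCM Oncology Department at two time points: baseline and day 5". That schedule also governs the primary outcome: the FACIT-F fatigue subscale is self-assessed "subscale at baseline and on day 5. FACIT-F is a well-validated quality-of-life instrument". The Discussion lists the absence of follow-up after the 5-day treatment as a limitation.
- **Contact by arm.** For the treatment group, SMI is given "by intravenous infusion once daily for 5 days as a period" (Intervention group). For the other arm: "Patients in the control group will receive only conventional therapy according to national guidelines" (Control group), with no duration or daily study contact given there. Patients and treating staff are not blinded (Randomization, allocation concealment, and blinding).
- **What the arms share.** "Patients will be recruited from the oncology inpatient department at each of the three GPHCM branch hospitals" (Setting and participants). Day-5 blood sampling for immunologic indicators and day-5 safety tests are described for participants without distinction by arm (Levels of immunologic indicators; Safety).
- **Expected loss and its handling.** The sample size is inflated "assuming a 20% dropout rate" (Sample size estimation). "If participants withdraw from the trial during the study period the reasons must be documented", and the same sentence adds a statistical analysis of the dropout rate (Quality control and trial management). Statistical analysis promises intention-to-treat and multiple imputation, but also excludes the data of patients who meet dropout criteria. Those criteria include serious adverse events, compliance below 80%, incomplete data and reluctance to continue.

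**The concern.** The primary comparison depends on a single observation per patient after baseline. Nothing in the text says how the score is obtained if the patient is not at the appointment, and there is no interim or later value to fall back on or to inform an imputation.

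The arms are not in the same position. An SMI patient who completes the course is in contact with study staff every day, and the last infusion falls at about the time of the assessment. No matching contact is stated for controls, who also know that they receive nothing extra. This makes it plausible that controls are lost more often.

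There is an opposite route. The exclusion criteria in Statistical analysis cover serious adverse events and low compliance. The Safety section describes reactions to SMI, and only SMI patients can miss infusions. That would remove SMI patients instead.

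If loss differs by arm, and the patients lost differ in fatigue from those seen, the estimated effect is biased. The stated exclusion of dropouts would carry that loss straight into the comparison. Power is a lesser matter, as the working shows.

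**Working it through.** **Inputs from the documents.** 47 patients randomised per arm; SD 7.28 in each group; target difference 4.95; two-sided 5%; 20% dropout, not split by arm (Sample size estimation).

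**Assumed inputs.** The documents give no loss rate by arm and no gap between missing and observed patients. Both are assumed below.

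**Step 1: the plan's own figures.** 38 / 0.8 = 47.5, against 47 per group as stated, so the dropout step reproduces apart from rounding (1 − 38/47 = 19.1%). The 38 itself does not reproduce at two-sided 5% and 90% power: the normal approximation gives 46 per group, and 38 is the one-sided result. That is a separate matter and does not bear on this point.

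**Step 2: effect of unequal loss on power.** Power = Φ(4.95 / SE − 1.96), with SE = 7.28 × √(1/n₁ + 1/n₂) and total loss held at about 20%.

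| Assumed loss, SMI / control | Assessed | Power |
|---|---|---|
| 20% / 20% | 38 / 38 | 84.2% |
| 10% / 30% | 42 / 33 | 83.2% |
| 5% / 35% | 45 / 31 | 83.0% |

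Power moves by about 1 percentage point, so the issue is bias.

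**Step 3: bias formula.** Let p be the share missing in an arm and D the mean of the missing minus the mean of the observed, with a positive D meaning that the missing are less fatigued. The observed mean then understates the arm's true mean by p × D. With the same D in both arms:

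bias in (SMI − control) = (p_control − p_SMI) × D

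The bias is zero if loss is equal or if D = 0. It favours SMI if controls are lost more often and the missing are better off. It changes sign if the missing are worse off, or if SMI patients are lost more often.

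**Step 4: illustrative range.**

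- Low end: 0.15 × 2 = 0.3 points; 0.3 / 4.95 = 6% of the target.
- High end: 0.30 × 6 = 1.8 points; 1.8 / 4.95 = 36% of the target.

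Only the difference in loss enters the formula. At 20% overall loss, a 15-point difference is for example 12.5% against 27.5%, and a 30-point difference is 5% against 35%.

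**Step 5: one worked case.** Loss 5% in SMI and 35% in control, D = 4:

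- bias = 0.30 × 4 = 1.2 points, 24% of 4.95
- assessed: 47 × 0.95 = 44.65 and 47 × 0.65 = 30.55
- SE = 7.28 × √(1/44.65 + 1/30.55) = 1.71
- shift = 1.2 / 1.71 = 0.70 SE
- false-positive rate = P(|Z + 0.70| > 1.96) ≈ 10.8%, against a nominal 5%

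With D = −4 the bias is −1.2 points. All these figures are for a complete-case difference, which is what excluding dropouts produces. They do not describe a multiple-imputation analysis, whose model the article does not state.

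**The case against.** The strongest reply is that nothing in the document shows that controls will be lost.

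- **Controls have reasons to be present.** They are recruited as inpatients, are undergoing chemotherapy and conventional therapy, and have day-5 blood and safety tests. This stands. A reader might infer that controls have no reason to attend, or would return only to fill in forms; the article does not support that. It does not remove the point either. Recruitment from an inpatient department is not a stated stay until day 5, and the day-5 tests fall at the same visit.
- **Early discharge is not in the document.** This stands. No discharge day or length of stay is given, so unequal loss is a possibility and not a fact.
- **The schedule may be in Fig. 2, and an article leaves detail to the full protocol.** Fair. The figure is not available here, so the text cannot establish that controls have no contact before day 5. What the point rests on is stated: one in-person assessment, no follow-up, a 20% allowance and the exclusion of dropouts.
- **The 20% is a dropout allowance, not a missed-visit rate.** Correct; it also covers adverse events, low compliance and deviations. It still means that the plan expects about one patient in five to leave the analysis within 5 days.
- **The split and the gap are chosen.** Correct. They illustrate the size and predict nothing, and a reading in which the bias must favour SMI is not supported.
- **A backup mode brings its own bias.** If remote completion is more common in one arm, mode is partly confounded with arm, and recording it cannot fully separate the two. This is a real cost, but likely smaller than having no score.

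**Conclusion.** The concern holds as a risk that the design leaves open. The day-5 appointment is the sole post-baseline source of the primary outcome, the plan expects 20% dropout, and it excludes dropouts while claiming intention-to-treat. Stated daily study contact exists in one arm only of an open-label trial, so loss can differ by arm.

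The size cannot be derived from the documents. The range of 0.3 to 1.8 points in either direction, 6% to 36% of the 4.95 target, rests on three assumptions: a 15 to 30 percentage-point difference in loss, a 2 to 6 point gap that is the same in both arms, and a complete-case comparison. With equal loss or no gap, the bias is zero.

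The change should be made, because it is cheap and protects against bias in both directions. Confidence is medium, since arm-specific loss is unknown and the full protocol may already contain a backup route.

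**What to change.** **Outcome measures and assessments.** Keep the in-person day-5 visit as the default and for the blood and safety tests. Add that the day-5 FACIT-F fatigue subscale and the other self-completed questionnaires are obtained on day 5 from every randomised patient, including those off site, those who stopped SMI and those who meet a dropout criterion. Where the patient is not on site, use a phone or electronic form and record the mode. Collection ends only when consent to data collection is withdrawn.

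**Statistical analysis.** Keep these scores in the intention-to-treat analysis and remove the exclusion of patients who meet dropout criteria from it. Without this second change the first achieves little, because the newly collected scores would be discarded. Multiple imputation then covers only scores that could not be obtained.

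**Cost.** A short amendment and a phone or electronic version of forms already in use; no extra visit. The primary outcome and four of the five secondary outcomes are self-completed, so most of the day-5 efficacy data can be recovered this way; the immunologic indicators cannot. The downside is a possible small mode effect that may be unbalanced by arm. A sensitivity analysis should examine it, for example by repeating the primary comparison in patients assessed in person and reporting mode by arm.
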